### Measures in Key Stakeholder Interviews

Semistructured interviews with adolescents who have completed the SMILE intervention, as well as with their parents or legal guardians, school professionals, and clinicians, will cover (1) the main concerns of children and young people; (2) perceived resources and coping supports; (3) feedback on the game from parents and school professionals; (4) perceived barriers to implementing SMILE tools at home and in school; and (5) perceived facilitators to implementing SMILE tools at home and in school.

### Process Evaluation

We will conduct a process evaluation to examine the implementation of the SMILE intervention and to understand what works, for whom, under what circumstances, and why. Quantitative data will describe outcome patterns and assess implementation and intervention fidelity, while qualitative data will help explain the underlying processes shaping these patterns. Using a mixed-methods realist evaluation approach[23], we will examine how contextual factors, implementation mechanisms, and outcomes interact within the adolescent population, as well as how broader socioeconomic and environmental factors influence engagement and decision-making. This approach will also enable us to explore how adolescents adapt SMILE to meet their individual needs.

### Data Analysis Plan

#### Proof-of-Concept Study

Hypotheses regarding the preliminary efficacy of the SMILE interventions will be examined using linear mixed-effects models (LMMs), fitted separately for each primary and secondary outcome. For outcomes assessed using age-specific scales, raw scores will be transformed to z scores or percentages to facilitate comparability across age groups. Models evaluating linear time-on-treatment effects will include fixed effects of time (calendar time and exposure time), condition (game with feedback, game without feedback, and baseline control), and the exposure time by condition interaction. We will also consider models including age and gender as covariates, with the final specification determined on the basis of model comparison. The random-effects structure will reflect the hierarchical design, with 3 levels: country, cluster, and individual. To account for outcome variability over calendar time, we will additionally include random effects for the cluster by calendar time and individual by calendar time components. Analyses will be conducted on the minimum-dose intention-to-treat sample, defined as participants who complete baseline assessments and at least one game module. Given the exploratory nature of this pilot, *P* values will be interpreted descriptively.

Adaptive interim analyses will be performed at the end of each sequence to estimate the empirical effects on primary and secondary outcomes. Predefined criteria for adjustment include potential changes to the primary outcomes, sample size, and intervention elements. First, if limited variance is observed in the primary outcomes of depression and anxiety, for example, if more than 80% to 90% of participants score within the top or bottom 10% of the scale, we will consider promoting well-being outcomes to the primary outcomes. This change would be accompanied by a recalculation of the required sample size based on the expected effect size for the revised primary outcome. Second, interim results may be used to adjust the planned sample size, including the number and/or size of clusters. Third, we will consider adaptations to intervention elements based on interim findings on engagement and the delivery of feedback, including changes to game modules or modes of interaction and adjustments to the level or detail of feedback provided in subsequent intervention sequences.

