**Results:**

The proof-of-concept trial was prospectively registered on April 29, 2025 (ISRCTN32523126). Study rollout is taking place from September 2025 to June 2026. As of March 2026, recruitment is ongoing, 2 study sequences have been completed, and the third sequence began at the end of March 2026. Primary results are expected in September 2026.

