### Proof-of-Concept Study

The overarching aim of the proof-of-concept study is to investigate the acceptability, feasibility, and preliminary efficacy of the gamified platform designed to enhance the well-being of adolescents and young adults in a pragmatic cluster randomized multisite multiarm adaptive trial. This study has 2 primary objectives. First is to investigate feasibility and acceptability in terms of reach (ie, participation, engagement, and adherence), preliminary efficacy operationalized as greater improvement of psychological distress, well-being, and resilience posttest, in the experimental conditions compared with the control period as the primary outcome, and engagement with the gamified intervention platform. This will provide the basis for assessing the public health impact of the use and engagement with the gamified platform. To provide context for the stated hypotheses, the SMILE intervention is delivered via 2 interconnected smartphone apps: the SMILE Game App (Nurogames and DigitalTwin Technology), which provides 5 modules of interactive CBT-based gameplay, and the SMILE Companion App (RDIUP), which facilitates self-monitoring, experience sampling methods (ESMs), and the collection of study metrics. Participating clusters are randomized to 1 of 2 intervention variants: a feedback condition or a no-feedback condition. While both groups engage with identical game content and monitoring assessments, participants in the feedback condition additionally receive automated, personalized data visualizations within the SMILE Companion App. These visualizations integrate in-game metrics, daily mood, and contextual data, aiming to enhance experiential learning, self-reflection, and the transfer of acquired skills to real-world contexts. A comprehensive description of these digital tools is provided in the “Methods” section. Specifically, we expect the following:

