The SMILE game aims to build resources and competencies without requiring players to disclose or explore personal negative experiences. However, gameplay may increase awareness of challenges in participants’ lives. While the game suggests coping strategies for some challenges, it does not address all possible difficulties. Participants (and legal guardians of minors) are informed in advance about available support services in their respective countries. An adverse event monitoring procedure has also been implemented. All adverse events occurring during the trial will be recorded, managed by the investigator as appropriate, and followed up. Events occurring after the completion of the study will also be documented if they are related to the intervention or study procedures. All adverse events and adverse device effects will be listed, statistically analyzed, and assessed by the sponsor for potential causal relationships with the investigation. The parties responsible for conducting the study meet regularly to monitor progress, review any adverse events, and oversee overall trial conduct. Additionally, a Data Monitoring and Ethics Committee has been established, comprising experts in Youth Mental Health, Clinical Trials, and Digital Interventions. The committee is independent from the sponsor and funder.

The proof-of-concept study was prospectively registered with the UK Clinical Study Registry (ISRCTN32523126) on April 29, 2025 by the chief investigator, before the enrollment of the first participant. A full statistical analysis plan will be registered before the end of recruitment and before data are available to the investigators. Any changes to the protocol will be transparently reported when disseminating study results.

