### Study Design

#### Proof-of-Concept Study

The protocol follows the SPIRIT (Standard Protocol Items: Recommendations for Interventional Trials) guidelines [52], with the checklist available in Checklist 1.

This proof-of-concept study uses a cluster-randomized, multisite, multiarm adaptive trial design. Participants are grouped into clusters (see Participants Recruitment and Procedure), which are allocated to 1 of 3 sequences based on feasibility. Each cluster is subsequently randomized to either feedback or a no-feedback variant of the intervention. Clusters assigned to Sequence 1 complete a neutral baseline period with ESM, followed by Game Modules 1‐2. Clusters in Sequence 2 complete the baseline period and Game Modules 1‐4. Clusters assigned to Sequence 3 complete the baseline period and all 5 game modules (Figure 1).

The adaptive trial design is based on an initial site-level sample size calculated under the assumption that all steps in the sequence will be completed. Two stages of adaptive interim analyses will be conducted to estimate the effects of each intervention modality, including the control condition. Based on these interim results, sample sizes per cluster or site may be adjusted and decisions may be made to amend or discontinue specific intervention elements. Each adaptive interim analysis will estimate effects on the primary outcomes and identify key predictors of these effects. Sample sizes and randomization sequences may be updated accordingly. Additionally, active intervention elements may be modified based on model parameters, including patterns of feature use and the contribution of intervention-related indicators to interim effect sizes. The trial will be complemented by a process evaluation [53], using a mixed-methods realist evaluation approach. This design enables the assessment of multiple aspects of the proof-of-concept study (ie, acceptability, feasibility, reach, and efficacy). In particular, it supports the estimation of efficacy with a low risk of bias (eg, by minimizing contamination between experimental and control periods), while also allowing for in-depth process evaluation and enhancing the generalizability of findings in a naturalistic field setting.

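### Well-being can become the primary outcome at an interim that also estimates effects by condition, on a trigger called predefined that has no single cut-off, time point or pooling rule

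*Protocol article*

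**What the plan says.** **Interims.** Study Design: "Two stages of adaptive interim analyses will be conducted to estimate the effects of each intervention modality, including the control condition". Data Analysis Plan: "Adaptive interim analyses will be performed at the end of each sequence to estimate the empirical effects on primary and secondary outcomes". Well-being is a secondary outcome, so its effect is among those estimated.

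**Rule for changing the outcome.** Data Analysis Plan: "Predefined criteria for adjustment include potential changes to the primary outcomes, sample size, and intervention elements". Limited variance in depression and anxiety is then illustrated by an example: "if more than 80% to 90% of participants score within the top or bottom 10% of the scale, we will consider promoting well-being outcomes". A new sample size calculation would follow.

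**Which outcomes are primary.** Hypothesis 1 and the Primary Outcomes section name anxiety and depression. Hypothesis 2 and the Secondary Outcomes section make well-being and resilience secondary. The aims paragraph that precedes the hypotheses instead describes preliminary efficacy as "greater improvement of psychological distress, well-being, and resilience posttest, in the experimental conditions compared with the control period as the primary outcome".

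**Timing of the SAP.** Ethical Considerations: "A full statistical analysis plan will be registered before the end of recruitment and before data are available to the investigators". The Abstract reports: "As of March 2026, recruitment is ongoing, 2 study sequences have been completed, and the third sequence began at the end of March 2026".

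**The concern.** A change of primary outcome during a trial can be defended when the decision cannot depend on treatment effects. Here three features leave that open.

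- The decision is taken at an analysis that also shows how well-being, depression and anxiety respond in each condition.
- The rule leaves room for judgement just where judgement would matter.
- The rule does not say which scores are counted, so a treatment effect could itself help to meet it.

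At stake is how far the headline result can be trusted. The findings are meant to inform a definitive trial, and an outcome chosen with knowledge of its interim effect gives an estimate that tends to be too favourable, however the P values are labelled. The aims paragraph adds to the difficulty: if well-being is already described there as part of the primary outcome, a later promotion is harder for a reader to detect. A registered SAP would be the natural safeguard, but the article does not make clear that it precedes the interim results.

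**Working it through.** **1. Is the trigger a fixed rule?** Four elements are open.

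- Cut-off: a band of 80% to 90%. With 85% of participants in the extreme zone, switching and not switching both comply.
- Force: the band is only an example, and meeting it leads to consideration, not to a decision.
- Data: no time point is named, and nothing says the scores are pooled over conditions.
- Scope: the text does not say whether depression, anxiety or both must meet it. Nor does it say how the check works across the age-specific instruments (PSWQ-C and GAD-7 for anxiety, PHQ-A and PHQ-9 for depression).

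**2. Can the trigger respond to treatment?** Inputs: an effect of 0.20 SD (Sample section) and the limits of 80% and 90% (Data Analysis Plan). Assumption, not from the document: symptoms follow a normal distribution and treatment shifts it by 0.20 SD towards fewer symptoms. If a share p lies in the low-symptom zone before the game, the share afterwards is Φ(z(p) + 0.20).

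| Share before | z(p) | z(p) + 0.20 | Share after |
|---|---|---|---|
| 79% | 0.806 | 1.006 | 84.3% |
| 86% | 1.080 | 1.280 | 90.0% |
| 88% | 1.175 | 1.375 | 91.5% |

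The expected effect alone carries 79% past the lower limit. It brings 86% to the upper limit and carries 88% past it. These are shares among post-start scores. Mixed equally with pre-game scores, the first row becomes (79 + 84.3)/2 = 81.6%, still past 80%. The third becomes (88 + 91.5)/2 = 89.8%, just short of 90%. The result therefore depends on which scores are counted and which limit is used, and the text fixes neither.

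**3. Hypothetical worst case for error.** The document states no rule that follows the interim effect. To bound the harm, suppose the switch did follow it: well-being replaces both primaries whenever its interim z value is the largest of the three. Assumptions: no true effect, equal correlations of 0.3 to 0.7 between outcomes, interim at two thirds of the information, success if the final z exceeds 1.96 in the favourable direction. By simulation:

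- A switch occurs in one third of trials, as symmetry requires.
- Given a switch, the error for well-being is about 5.0% to 6.1%, against 2.5% for one outcome fixed in advance.
- Over all trials, with success on either of two unadjusted primaries, error is 4.2% to 4.8% without switching and 5.1% to 6.4% with it. The ratio is 5.1/4.2 = 1.2 to 6.4/4.8 = 1.3.

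**4. Timing of the SAP.** Three statements stand side by side: registration is to come before investigators have data; an effect-estimating interim follows each sequence, and its findings can change later ones; two sequences were complete by March 2026. They agree in only two cases. Either the SAP was registered before the first interim, or the investigators do not see interim results. The article states neither. The Data Monitoring and Ethics Committee is independent of sponsor and funder, but is given no stated part in this decision.

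**The case against.** **The trigger is about distribution, not effect.** This is true, and a floor effect in a largely healthy sample is a sound reason to reconsider an outcome. But a distribution trigger protects only if it is fixed and read from data that treatment cannot have altered, and neither is stated.

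**The study is exploratory.** P values are to be read descriptively and no alpha adjustment is made. This stands, and it makes a false-positive rate a poor main yardstick. A reader might infer that the plan more than doubles the false-positive rate. The documents do not support that: the figure is conditional on a switch, assumes an effect-driven rule that the protocol does not contain, and is set against a single outcome. Against the two unadjusted primaries, overall error rises by about a fifth to a third. Selective choice of the headline outcome remains a concern under descriptive reading.

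**The SAP promise may have been kept.** A reader might infer that the SAP cannot precede data availability, since "2 study sequences have been completed". The documents do not show this. They do not say whether the SAP was already registered, whether the interims were run, or who saw them, and the future tense is normal in a protocol. For the same reason the authors should not be told to declare that the SAP followed the interim data. Nor is reporting Sequence 3 separately a simple remedy: it has five modules rather than two or four, and clusters enter sequences by feasibility, not by randomization.

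**The aims sentence is loosely worded.** The Abstract, the hypotheses and both outcome sections agree with one another. The contradiction is minor, but it concerns the very outcome that may be promoted.

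**Conclusion.** The concern holds for the outcome-change rule. The text allows well-being to be promoted at an interim that estimates effects by condition, on a trigger with no single cut-off, time point or pooling rule, although it is called predefined. The document does not show that a switch has been or will be made because of an effect; it shows that nothing in the stated rule prevents this.

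The size is best expressed by the trigger's sensitivity: an effect of 0.20 SD moves 79% to 84% and 86% to 90% if post-start scores count, on the normal-shift assumption. The error figures are a worst case only and rest on assumed correlations and interim timing.

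The aims paragraph does contradict Hypotheses 1 and 2. On the SAP, the finding is an unresolved tension that the authors can settle with one statement. The changes should be made, but the trial's exploratory purpose keeps this short of a fatal flaw.

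**What to change.** 1. **Trigger.** Replace the band with one fixed cut-off per instrument, for example more than 80% of participants in the extreme 10% of the scale. Apply it to T0 scores pooled over conditions. State whether one or both primary outcomes must meet it.
2. **Order of decisions.** Take and record the decision before any by-condition output is produced. If such output already exists, say so when reporting.
3. **Reporting.** Report anxiety and depression as the original primary outcomes in every case. If well-being is promoted, take its completeness into account: secondary questionnaires are optional, while the primary measures are mandatory at T0 and T1.
4. **Aims paragraph.** Align it with Hypotheses 1 and 2, so that well-being and resilience are named as secondary.
5. **SAP.** State whether it was registered before the first interim, or how the investigators are kept from interim results. If neither applies, withdraw the statement.

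The cost is a few sentences in the protocol and SAP, and less freedom to change the outcome later. T0 scores are mandatory for the primary outcomes, so no extra data collection is needed.

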#### Key Stakeholder Interviews

Interviews will be audio-recorded and transcribed. Qualitative data will be analyzed using qualitative data analysis software (eg, MAXQDA [VERBI Software] 2022 [71]). We will apply an inductive thematic analysis [72], involving familiarization with the data, systematic coding of relevant segments, identification of candidate themes, and iterative review and refinement of themes against the coded extracts and the full dataset. Themes will then be defined and named to produce a coherent thematic account. Analyses will first be conducted within each pilot site to generate site-level themes reflecting participants’ needs, experiences, and perceived best practices. These findings will subsequently inform a cross-national synthesis. An English-language report will be produced to summarize the results and support the interpretation of study outcomes and future implementation planning. Finally, quantitative data will include demographic characteristics, which will be summarized using descriptive statistics.

## Results

As of March 2026, a total of 46 clusters have been recruited, and 2 sequences have been completed. The third sequence commenced in the final days of March 2026, with clusters planned to join on a rolling basis. Primary results are expected in September 2026.

## Discussion

The SMILE project contributes to ongoing global efforts to improve the mental health and well-being of adolescents and young adults through scalable digital interventions. By delivering the intervention through a gamified smartphone app, the project aims to increase accessibility and reduce barriers to participation [6,10,14,18,23,28]. Smartphones are widely used by adolescents and young adults, and gamified environments are familiar to this population. Leveraging these existing habits may facilitate engagement and support implementation in real-world settings. The intervention is grounded in CBT principles and focuses on strengthening personal resources and coping strategies. This approach allows the program to be implemented as a universal intervention across diverse demographic and sociocultural contexts. Gamification may also help reduce some of the demands associated with traditional digital mental health interventions [73]. Presenting intervention content through intuitive game mechanics may facilitate participation among users with varying levels of cognitive and digital literacy. Furthermore, by conducting the study across 7 European countries, the SMILE project may provide insights relevant for broader implementation in Europe. SMILE has been cocreated through a multistep process that included initial focus groups with adolescents and young adults, their parents, as well as school and clinical professionals. This was followed by a Living Labs testing phase [74], during which target users provided feedback on the intervention prototype. Such a participatory approach was intended to support the development of an intervention that is relevant, usable, and engaging for the target population. The stage of SMILE described in this protocol represents a continuation of this iterative development process, focusing on feasibility and acceptability, alongside preliminary efficacy, to inform further refinement of the intervention. The results of the study will be disseminated to multiple stakeholder groups. Findings will be reported in trial registries and shared through peer-reviewed publications and conference presentations targeting the scientific and health care communities. Where appropriate, summaries of the results will also be made available to participants and the broader public in accessible, plain-language formats.

Several limitations should be acknowledged. First, recruitment followed a pragmatic approach, and participating schools were primarily selected based on availability. Consequently, the study samples may not be fully representative of the broader populations within the participating countries. Second, in addition, due to time constraints, not all feedback collected from participants during adaptive interim analyses will be implemented within the study phase. Third, SMILE is implemented as an unguided intervention and primarily relies on automated reminders from the SMILE Companion App to prompt participants to complete study measurements and progress through the game. Additional reminders encouraging participants to log into the app are sent via email by the research teams at each study site. While this approach supports the accessibility and scalability of the intervention, it may also increase the risk of participant dropout. Fourth, the study relies on the assumption that all participants have access to mobile devices for the duration of testing. While some pilot sites (United Kingdom and Slovenia) were able to offer devices to participants to facilitate participation, the study will likely not be fully representative of the broad range of digital literacy in adolescents and young adults as a result. Finally, although some objective measures are included, the primary outcomes rely on self-reported data, which may be subject to reporting bias.

In conclusion, if SMILE is found to be feasible, acceptable, and to show preliminary efficacy, it may offer a scalable and accessible tool to support the mental health and well-being of adolescents and young adults. Such an intervention could be implemented either as a stand-alone resource or as part of broader support systems, including school-based or health care–based mental health services.
